#### Student and school staff participants

Schools assigned to the school-led You-CAN and research-led You-CAN arms will deliver the intervention. Within these schools, one or two school staff members will be recruited to participate in this study. School staff will be made aware of the study through direct communication with their school’s principal. In addition, two or more students will be recruited to participate in their school’s Concussion Council, and will be made aware of the study through their school principal and participating school staff member(s). All students at the participating schools will be made aware of, and invited to participate in, the school-wide administration of the CRSS-M.

#### Informed consent

Figure 3 contains an overview of the study consent procedures. Principals will provide active consent on behalf of their school to participate in the study. School staff will provide active consent to participate. Parents/guardians of students participating in the Concussion Council will provide active consent for their child to participate, and students in the Concussion Council will provide assent. A school-wide information letter will be sent to all parents/guardians at the participating school to inform them of the school-wide administration of the CRSS-M, and students will actively consent to participate in the school-wide survey. Consent can be withdrawn at any time and will not affect the participant’s relationship with the school board or the research team.

**Fig. 3 Fig3:**
[figure not shown]
Study participant consent procedures

### The You-CAN intervention

#### Theory

You-CAN has been developed using a service learning educational approach. According to this approach, students learn new knowledge and skills by performing community service activities [18]. Service learning is mutually beneficial to both students and the community [18, 33–35], and high school aged youth who participate in service learning have shown an increase in personal and social responsibility, transferable skills, and academic achievement [18]. Service learning allows students to learn through experience while advocating for the needs of their community [18]. The You-CAN intervention will follow the Investigation, Plan and Prepare, Action, Reflection and Demonstration (IPARD) model of service learning (Table 1) [36].

**Table 1 Tab1:** The You-CAN intervention outlined using the IPARD Model of Service Learning [36]

IPARD Stage	Description
Investigate (I)	Investigate the need for concussion awareness and create concussion councils to address change
Plan and Prepare (P)	Plan and Prepare for concussion awareness campaign
Action (A)	Act by leading a week-long concussion awareness campaign
Reflect (R)	Reflect on experiences as a council member with the research team
Demonstrate (D)	Demonstrate and celebrate impact at the *Rowan Stringer Concussion Awareness Showcase*

### Delivery

#### Concussion councils

You-CAN will be delivered by a group of high school students and school staff member(s) referred to as a Concussion Council. The main goal of the Concussion Council is to plan and deliver a week-long concussion awareness campaign at their school. The Concussion Council will meet regularly (timing to be determined based on group preference) throughout the school year, and must have a minimum two students that are supported by one to two school staff. There is no maximum to the number of students who can be involved in the council.

#### You-CAN web portal

The *You-CAN Web Portal* has been developed by the research team, and contains evidence-based concussion resources [37], as well as instructions and timelines for the Concussion Council. Each participating school will have a unique login for the *You-CAN Web Portal*, allowing each Concussion Council to upload documents to their account. The *You-CAN Web Portal* will also be used as a method of communication with the research team and include functionalities such as email and video-calling. The *You-CAN Web Portal* will also contain an instructional handbook for school staff participants.

#### Concussion awareness campaign

The Concussion Council will run a week-long concussion awareness campaign. Creativity is encouraged and Concussion Councils will implement their own unique ideas that they believe will raise awareness in their school environment. There are no mandatory structured activities that must be done during the concussion awareness campaign. Any information about concussion being shared in the campaign must come from the resources on the *You-CAN Web Portal* that have been reviewed for content accuracy. If a school creates or finds a new resource for their campaign that is not on the *You-CAN Web Portal* then the resource must be approved by the research team prior to inclusion in the concussion awareness campaigns.

#### Rowan stringer concussion awareness campaign showcase

After completing a concussion awareness campaign, Concussion Councils will be invited to participate in *The Rowan Stringer Concussion Awareness Campaign Showcase.* Rowan Stringer was a high school student who passed away due to head injuries experienced playing rugby, and as a result, *Bill 193 – Rowan’s Law (Concussion Safety)* was passed in 2018 as a means to raise awareness about concussion in the province of Ontario, Canada [38]. *The Rowan Stringer Concussion Awareness Campaign Showcase* is a half-day event that will take place online through the platform Zoom [31]; with the goal of sharing and celebrating each school’s concussion awareness campaign with other participating schools from across Canada. Each school will be given 5–7 min to present highlights from their awareness campaign using a standardized PowerPoint presentation template. This portion of the intervention acts as the demonstration phase of the IPARD Model [36] outlined in Table 1.

### Outcome measures

The instruments and data collection tools selected, as well as the timeline for implementation are found in Table 2. All data will be de-identified and stored on a secure network. Only the research team will have access to the final dataset.

**Table 2 Tab2:** You-CAN intervention and data collection timeline

	2019				2020				
	Sept	Oct	Nov	Dec	Jan	Feb	Mar	Apr	May
Informed consent: principals, school staff, council members	X								
Intervention time points									
Concussion awareness campaign						X	X		
*Rowan Stringer Concussion Awareness Campaign Showcase*								X	
Monthly video call with research team^*a*^		X	X	X	X	X	X	X	X
Outcome Measures									
School environment survey		X							
Concussion Reporting and Social Support Measure (CRSS-M) (T_0_)		X							
Web portal analytics		X	X	X	X	X	X	X	X
Field notes from monthly video calls^*a*^		X	X	X	X	X	X	X	X
Campaign details survey					X				
Content created					X	X	X	X	
Additional activities tracking sheet								X	
Post-showcase evaluation survey								X	
Exit interviews									X
Concussion Reporting and Social Support Measure (CRSS-M) (T_1_)									X

^*a*^*Only applies to the You-CAN led by school staff and research team arm*

### Primary outcome measures

The primary outcome of interest is the CRSS-M, which measures an individual’s intent to report a concussion to an adult and intent to provide social support to a peer who has experienced a concussion. Responses on the CRSS-M may be influenced by factors captured using the school environment survey and additional activities tracking sheet.

#### Concussion reporting and social support measure (CRSS-M)

The CRSS-M is an outcome measure developed and piloted by the research team that will be delivered to students at the beginning {T_0_} and end {T_1_} of the school year, pre- and post-participation in You-CAN. The CRSS-M was informed by the Theory of Planned Behaviour [12] and includes questions regarding demographic information (i.e. concussion history, sport participation, etc.), concussion knowledge, attitudes, perceived behavioural control, subjective norms, intent to report concussion symptoms to an adult and intent to provide social support to a peer. The CRSS-M also contains a 6 question unique identification code that allows individual surveys to be anonymously linked. It contains 57 questions including yes/no, multiple choice, checkbox, open-ended, true/false and Likert scale questions and will take approximately 10 min to complete. The CRSS-M was developed in order to provide questions about concussion that are relevant for a wide variety of high school students (sport and non-sport related questions).

#### School environment survey

The school environment survey contains questions regarding the demographics of the school population (i.e. school population, socioeconomic status, average class size) and has been developed by the research team. The school environment survey contains checkbox, yes/no, multiple choice, and open-ended response questions. This survey will be completed by school principals in all arms of the study at the beginning of the school year. This will provide important context about the different participating school environments, which will be used when interpreting CRSS-M results.

#### Additional activities tracking sheet

Concussion Councils will complete an additional activities tracking sheet that documents the dates and a brief description of any additional awareness building activities they complete outside of their week-long concussion awareness campaigns throughout the school year. This will be submitted to the research team prior to the end of the school year. Completing additional activities is not required or recommended; however, if Concussion Councils complete additional awareness building activities, it will be required for them to document the activities and will be used to provide important contextual information when interpreting CRSS-M results.

### Secondary outcome measures

The secondary outcome of the study is to understand the implementation fidelity, acceptability, and student and school staff experiences with the You-CAN intervention using the outcome measures described below.

#### You-CAN web portal analytics

Google Analytics [39] data for the *You-CAN Web Portal* domain will be downloaded on a monthly basis throughout the duration of study. This will provide data on number of users, average time on pages, location of users, operating system and devices used to access the web portal, bounce rates, behaviour flow, in-page analytics, traffic sources, form abandonment, form submissions, and how often pages were printed.

#### Field notes from monthly video calls

Field notes will be recorded using a standard template during monthly video calls with the research-led schools. Research team members will record their initial thoughts and reactions to the call, key questions asked by students, and observations. Items such as length of call, number of students present and technical issues will also be recorded.

#### Campaign details survey

The campaign details survey was developed by the research team and will be completed by Concussion Councils approximately 2 weeks prior to the delivery of their concussion awareness campaign. The survey consists of yes/no and open-ended response questions related to the planned activities for the concussion awareness campaign. Examples include: What knowledge sharing events do you have planned? Where will the event happen? Who will be involved? And what information about concussion will be provided?

#### Content created by concussion councils

As councils are encouraged to be creative when developing their concussion awareness campaigns, it is anticipated that some Concussion Councils may create new resources (i.e. videos, images, infographics) to be disseminated to their school community. These resources will be reviewed for content accuracy by the research team prior to distribution, and will be collected as data. The PowerPoint presentation that Concussion Councils create and present at the *Rowan Stringer Concussion Awareness Campaign Showcase* will also be collected.

#### Post-showcase evaluation survey

After participating in the *Rowan Stringer Concussion Awareness Campaign Showcase,* student and school staff participants will be invited to complete the post-showcase evaluation survey within 2 weeks of the event. The survey consists of thirteen Likert scale questions, one multiple choice question, and one open-ended question. The purpose of the post-showcase evaluation survey is to understand participants’ experiences and suggestions to improve the event.

#### Exit interviews

Iterative semi-structured interviews will be completed with both the Concussion Council and school staff participants. As focus group interviews have been recommended as an ideal methodology to evaluate concussion education programs [18], interviews with Concussion Council members will use a focus group format through the platform Zoom [31]. School staff interviews will be completed individually over the telephone. Interviews and focus groups will be guided by the five stages of the IPARD model [36]. The purpose of these interviews is to allow for a deeper understanding of the student and school staff experiences participating in You-CAN. Interviews will be audio recorded and transcribed verbatim.

### Data analysis

#### Hypothesis 1

To examine the first research hypothesis, the following analyses will be performed. Data from the CRSS-M will be screened for outliers, and items will be screened for multicollinearity. CRSS-M data will be included for analysis if 90% of questions per section are answered and if there are matching unique identification codes from pretest {T_0_} to posttest {T_1_}. Descriptive statistics will be used to analyze demographics, true/false, checkbox and Likert scales responses. Paired sample t-tests will be used to detect changes in individual responses at pretest {T_0_} and posttest {T_1_} time points. A repeated measure ANOVA will be used to investigate differences in the 3 study arm schools (school-led You-CAN, research-led You-CAN and comparison group) from pretest {T_0_} and posttest {T_1_}. Co-variate adjustments will be completed depending on baseline means. Change scores from each You-CAN study arm will be compared across factors using a multifactorial ANOVA. Post-hoc tests (α = 0.05) will be used to determine the mean differences between each study arm. The school environment survey data will be analyzed through a descriptive univariate analysis. To determine the influence of school factors and additional activities completed by the Concussion Councils on CRSS-M change scores, co-variate adjustments and a multifactorial linear regression will be completed. Statistical analyses will be completed using SPSS [40]. Equivalent non-parametric approaches to analyses will be used should the data not meet necessary assumptions (e.g., normal distribution etc.).

#### Hypothesis 2

To examine the second research hypothesis (H_2_), the following analyses will be performed. A descriptive univariate analysis of web portal analytic data will be completed, and compared across time. Research field notes from monthly video calls will be analyzed using categorical descriptive statistics, and content of open-ended questions will be coded and counts will be reported across coded domains. Campaign details surveys will be analyzed using descriptive statistics and frequencies. Open-ended responses will be coded and coded domains will be reported as counts (frequencies and percentages). All items created by Concussion Councils (resources, showcase presentations) will be analyzed using a content analysis [41]. This includes identifying patterns across information and visual mediums in a replicable and systematic manner, and has been used to evaluate concussion resources [42, 43]. A customized coding scheme will be developed by randomly selecting a small number of resources to be assessed prior to data analysis in order to develop and refine the coding scheme (e.g. type of image, primary content of image, purpose of image, information quality). Post-showcase survey Likert scale questions will be reported as frequencies and percentages. Open-ended questions will be coded and categorized and codes will be reported as frequencies. All exit interviews with student and school staff participants will be analyzed using a deductive thematic analysis [44]. Two independent researchers will review transcripts and generate codes across all interviews. To ensure rigour, a third member of the research team will consult at each stage of the comparative analysis to ensure the codes and themes are representative of the data. Through these analyses, information will be provided about the acceptability of the You-CAN intervention.

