**Methods:**

This longitudinal study will use a cluster randomized trial design. Three high schools from six randomly selected Canadian school boards will participate and be randomized to three study arms: (1) You-CAN led by school staff; (2) You-CAN led by school staff and research team; and (3) untreated comparison group. Intervention arms 1 and 2 will deliver the You-CAN program and create a Concussion Council at their school. The Concussion Council will deliver a concussion awareness campaign and participate in an online showcase with other participating schools. In addition, arm 2 will have monthly video-calls with the research team. A survey based on the Theory of Planned Behaviour will be administered school-wide with all arms (1, 2, 3) at two time points (beginning {T_0_} and end {T_1_} of the school year). Exit interviews will be completed with the Concussion Councils and participating school staff.

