### Sample size

A sample size calculation was completed based on pilot administration of this study’s main outcome measure, the Concussion Reporting and Social Support Measure (CRSS-M) (see Outcome Measures section below). The sample size was calculated using an effect size of 0.20 (α = 0.05 and power = 0.80). This is in line with previously estimated effect sizes for school-based interventions conducted with high school aged youth [26–28]. As the CRSS-M is being administered in the school-setting with support from participating school boards, principals and school staff, we expect a low attrition rate (about 10%) from the beginning {T_0_} to end {T_1_} of the school year. Based on this information, we require 140 participants to complete the survey at each participating high school.

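### Limiting the Hypothesis 1 analysis to code-linked students with 90% of questions per section answered discards usable surveys, selects students after allocation, and is not covered by the 10% planned for attrition

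*Protocol article*

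**What the plan says.** The Data analysis section of the protocol article (Hypothesis 1) fixes the analysed set: "CRSS-M data will be included for analysis if 90% of questions per section are answered and if there are matching unique identification codes" from T0 to T1. The tests named there include paired t-tests, a repeated measures ANOVA and analyses of change scores, all of which need both answers from the same student. No other analysis set is named.

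The CRSS-M section describes the linkage: "The CRSS-M also contains a 6 question unique identification code that allows individual surveys to be anonymously linked". On length it says: "It contains 57 questions including yes/no, multiple choice, checkbox, open-ended, true/false and Likert scale questions". It lists demographics and six constructs (knowledge, attitudes, perceived behavioural control, subjective norms, and the two intents), but not the number of items in each.

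The Sample size section states: "we expect a low attrition rate (about 10%) from the beginning {T_0_} to end {T_1_} of the school year". It concludes: "we require 140 participants to complete the survey at each participating high school". The reason given for the low figure is the support of boards, principals and staff for running the survey.

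On design, the abstract's Methods paragraph says: "Three high schools from six randomly selected Canadian school boards will participate and be randomized to three study arms". The section on student and school staff participants says that all students in these schools are invited to take the survey. Table 2 places T0 in October and T1 in May.

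**The concern.** The unit of randomisation is the school, so a student's arm is known from the school without any personal code. A T1 survey that cannot be linked, or has a blank in one section, is still a valid observation from a randomised school. The rule removes it, and a failed code removes that student's T0 survey too.

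Two things are at stake. The first is selection. Table 2 and the Intervention assignment section imply that schools are allocated before the October survey, because council members are recruited only in intervention schools and consent in September. Reproducing one's code and filling in every section therefore happen after allocation. Intervention schools have a council and involved staff, and comparison schools do not. If that changes who links or completes, the arms are compared on differently selected students, and more respondents would not cure this.

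The second is planning. The allowance of about 10% is described as attrition between waves and justified by school support. That reasoning covers whether students are surveyed again, not whether their codes agree or their sections are full.

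**Working it through.** **1. The plan's own figure.** Stated inputs (Sample size): "The sample size was calculated using an effect size of 0.20 (α = 0.05 and power = 0.80", with 140 per school, about 10% attrition and 6 schools per arm. A two-sided comparison of two means at a standardised difference of 0.20 needs 393 per arm. That is 393/6 = 65.5 per school, and 65.5/0.9 = 72.8, so 73 per school. The figure of 140 is not reached without unstated inputs. With a design effect of 1 + (m − 1) × ICC and an ICC of about 0.0074, 127 per school are needed, and 127/0.9 = 141. The test and the ICC are not given, so 140 is not called wrong here. The only step used below is 140 × 0.9 = 126 retained per school.

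**2. What 90% per section allows.** Blanks allowed in a section of k items = k − ceil(0.9k).

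- k = 2 to 9: none (at k = 9, one blank gives 8/9 = 0.889, below 0.90)
- k = 10 to 19: one
- k = 20 to 24: two

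Taking the listed areas as the sections (an assumption), the mean size is 57/7 = 8.1, or 51/7 = 7.3 if the six code questions are among the 57. With six sections it is 57/6 = 9.5. On each count at least one section has 9 or fewer items and tolerates no blank. Longer sections, if there are any, tolerate one or more.

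**3. Linkage (assumed rates).** If each of the six code answers repeats with probability p, independently, an exact match has probability p^6:

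| p | match, p^6 | total loss, 1 − 0.9 × p^6 |
|---|---|---|
| 0.99 | 94.1% | 15.3% |
| 0.98 | 88.6% | 20.3% |
| 0.95 | 73.5% | 33.8% |

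These losses come before any item rule.

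**4. Total loss (assumed rates).** Retained = 0.90 × linkage × completeness. Pairs are per 140 surveyed; the fourth column is 126/retained, rounded up. Power is for a difference of 0.20 at the ICC of about 0.0074 from step 1, by the normal approximation.

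| linkage / completeness | loss | pairs per school | surveyed to keep 126 | power |
|---|---|---|---|---|
| 100% / 100% | 10.0% | 126 | 140 | 0.80 |
| 95% / 95% | 18.8% | 114 | 156 | 0.78 |
| 90% / 90% | 27.1% | 102 | 173 | 0.75 |
| 80% / 80% | 42.4% | 81 | 219 | 0.70 |

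Given 10% attrition, the loss stays at 10% only if every code matches and every section passes.

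**The case against.** The strongest reply is that linked pairs are what a longitudinal design with paired tests calls for, that the code was built for this purpose, and that the same survey and code are used in every arm. The numbers may also not suffer: 140 is a requirement, not a cap, and all students are invited. Even with linkage of only 60% (assumed) and 10% attrition, 126 pairs need 126/(0.9 × 0.6) = 233 surveyed students, which is 58% of a 400-student school.

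Much of this stands, and it rules out four stronger readings.

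- A reader might infer that 90% means no missing item at all. That is proven only for sections under 10 items, and section sizes are not given.
- A reader might infer that one failed section removes the whole survey. The phrase can equally mean that each section is admitted on its own, which loses far less. If all 57 items were needed at both waves, independent blanks at an assumed 0.5% per item would leave 0.995^114 = 56% of pairs. That is a worst case under one of the two readings, and blanks that cluster in the same students would cost less.
- A reader might infer that the loss will exceed 10%, or that 126 per school will not be reached. The documents give no match rate and no blank rate, and large schools can survey more than 140.
- A reader might infer that the arm comparison is biased. Nothing in the documents shows that linkage or completeness will differ by arm.

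Two parts of the reply do not carry. Extra respondents repair precision, not selection, and schools of 100 to 139 students are eligible (School recruitment) but cannot supply 140. Nor is this a detail left to a later plan: the article states the rule.

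**Conclusion.** The point holds in a limited form. The stated rule discards T1 answers whose arm is known and defines the analysed set by student behaviour after allocation. It tolerates no blank in any section under 10 items, and at least one section is that short if the listed areas are the sections.

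The 10% covers attrition alone. If that attrition occurs, any failed link or failed section takes the loss above 10%: about 19% to 27% in the two milder scenarios, 42% in the harshest one shown. These rates are assumptions. The accompanying fall in power, from 0.80 to between 0.78 and 0.70, also rests on an ICC inferred from the figure of 140, so it is indicative only and would be smaller where schools survey more than 140 students. The risk of selection bias matters more than the power loss; its size and direction are unknown. The change is worth making because it is cheap.

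**What to change.** Change the Hypothesis 1 analysis text and one line of the sample size:

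- Apply the completeness criterion separately to each outcome scale, so that a blank in one section does not remove the others. State the number of items in each scale.
- Make the primary analysis a mixed model on all available T0 and T1 surveys, with arm, time and their interaction, a random effect for school and, where surveys are linked, one for student.
- Keep the linked, 90%-complete set as a sensitivity analysis.
- Report the matched fraction by arm.
- Restate the 10% as total loss, including non-linkage and item loss, with the rate assumed for each.

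No extra data collection is needed for the analysis changes; a larger loss allowance may raise the number of students to be surveyed per school. The cost is some additional modelling. Unlinked surveys carry less information about change, and an unlinked student's two surveys are treated as independent within the school. The model also does nothing about students who never take the survey.
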